9. **Haematology:** Blood samples will be collected for haematology assessments (including RBC Count, haemoglobin, haematocrit, MCV, MCH, MCHC, platelet count, TLC and DLC) at screening visit (any time from D-14 through D-1), D28, D56, D180, D208 and D365. Haematology assessments done at Screening Visit (Visit 2) will be considered as screening laboratory assessments for eligibility as well as baseline assessments for safety end-points since haematology assessments will not be done on Day 0 (pre-vaccination). Blood samples for haematology will be collected prior to vaccination on Days 28 and 180.
10. **Serum Chemistry:** Blood samples will be collected for serum chemistry assessments (including potassium, sodium, AST, ALT, direct, indirect and total bilirubin, alkaline phosphatase,  $\gamma$ GT, creatinine, random blood glucose) during screening period (D-14 through D-1), D28, D56, D180, D208 and D365. Serum chemistry assessments done at Screening Visit (Visit 2) will be considered as screening laboratory assessments for eligibility as well as baseline assessments for safety end-points since serum chemistry assessments will not be done on Day 0 (pre-vaccination). Blood samples for serum chemistry will be collected prior to vaccination on Days 28 and 180.

*Information contained in this publication is the property of EVI and ICGEB and is confidential and will not be disclosed to third parties without written authorization from EVI and ICGEB. No part of this document may be reproduced, stored in a retrieval system or transmitted in any form or by any means -electronic, mechanical, recording or otherwise - without the prior authorization of EVI and ICGEB*

[figure not shown][figure not shown]

11. **Direct Coomb's Test:** Direct Coomb's test will be undertaken at Screening Visit (Visit 2) and additionally will be done during the entire study period if the haemoglobin falls below 13 gm/dL.
12. **Peripheral Blood Smear (PBS):** PBS examination will be undertaken for evidence of haemolysis or any haematological disorder at Screening Visit (Visit 2) and additionally during the entire study period along with Coomb's test if the haemoglobin falls below 13 gm/dL.

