## 4.6 Definition of Study Endpoints

### 4.6.1 Primary Endpoint(s)

The safety profile will be assessed on the basis of the following criteria

- Immediate reactogenicity (any event occurring within the first three (3) hours recorded every 30 minutes after each vaccination, with emphasis on allergic reactions)
- Local and systemic reactogenicity (solicited adverse events occurring from three (3) hours post-vaccination on Day 0 till Day 14 after each dose)
- Any unsolicited adverse events 28 days after each vaccination
- Any Serious Adverse Event (SAE) occurring from the first dose of vaccine till the last follow-up visit.
- Biological safety, 28 days after each vaccination, in reference with the baseline before the first dose, by measuring the following parameters:

- Haematology: RBC count, Haemoglobin\*, Haematocrit/Packed Cell Volume (PCV), MCV (Mean Corpuscular Volume), MCH (Mean Corpuscular Haemoglobin), MCHC (Mean Corpuscular Haemoglobin Concentration), Platelet Count and Total Leukocyte Count (TLC) along with Differential Leukocyte Count (DLC) on Days -14, 28, 56, 180, 208, 365.

\*If the haemoglobin drops below 13 gm/dL, then a direct Coomb's test and a peripheral blood smear/film will be prepared and examined for evidence of possible haemolysis.

- Serum Chemistry: Potassium, Sodium, AST, ALT, Direct, Indirect and Total Bilirubin, Alkaline Phosphatase, Gamma Glutamyl Transpeptidase ( $\gamma$ GT), Creatinine, and Random blood glucose on Days -14, 28, 56, 180, 208, 365.

The Investigator will be responsible for causality assessment i.e. assessment of the relationship of the AE to the assigned study vaccines, using the following definitions: related or not related.

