#### 5.4.2 Exclusion Criteria

*The subjects will be excluded from study entry, if any one or more of the following criteria exist at the time of the Screening/Baseline Visit:*

1. Subject with evidence of IgG antibodies against PfMSP-119 and Pff2 as measured by ELISA
2. Subject with prior history of immunisation with Hepatitis B vaccine
3. Subject with known history of malaria
4. Subject with history of allergic reactions, hypersensitivity or anaphylaxis to any of the components of the study vaccines (JAIVAC-1 – Montanide ISA 720 malaria vaccine or Hepatitis B vaccine) (including adjuvant or peptide) or with history of serious allergic reactions to any substance, requiring hospitalisation or emergency medical care
5. Subject with previous vaccination with any other malaria candidate vaccines
6. Subject with use of an investigational or non-registered drug or vaccine other than the study vaccines within three (3) months preceding the first study vaccination, or planned use during the entire clinical trial period
7. Subject, who receives any vaccination or gamma globulin during the three-month period prior to the first vaccination
8. Subject with chronic administration (defined as more than 14 days) of immuno-suppressants or other immune-modifying drugs within six months prior to the first vaccination. This includes any dose level of oral steroids or inhaled steroids, but not topical steroids
9. Subjects will be excluded if AST > 40 IU/L, ALT > 41 IU/L,  $\gamma$  GT > 71 IU/L, Total Bilirubin > 1.2 mg/ dL, Indirect Bilirubin > 1.2 mg/ dL, Direct Bilirubin > 0.4 mg/dL, Serum Creatinine > 1.2 mg/ dL (Appendix B and B-1).
10. Subjects will be excluded in case of out of range values for the following parameters: Hemoglobin 13 to 18 g/ dL, RBC count  $4.0$  to  $7.0 \times 10^6/\mu\text{L}$  TLC  $4.0$  to  $11.0 \times$

*Information contained in this publication is the property of EVI and ICGEB and is confidential and will not be disclosed to third parties without written authorization from EVI and ICGEB. No part of this document may be reproduced, stored in a retrieval system or transmitted in any form or by any means -electronic, mechanical, recording or otherwise - without the prior authorization of EVI and ICGEB*

[figure not shown][figure not shown]

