## 7 STUDY CONDUCT, ASSESSMENTS AND VISIT PROCEDURES

### 7.1 General Aspects

This is a phase I, randomised, controlled, dose-escalating, single-blind clinical study for assessment of the safety and immunogenicity of the JAIVAC-1 – Montanide ISA 720 in healthy Indian male subjects between 18 to 45 years of age.

There are two (2) discreet informed consent documents for this study. Following the signing of the pre-screening informed consent form, each subject will be assigned a unique screening number. Thereafter, the required blood sample for testing for anti-malarial antibodies by ELISA will be drawn. Only if the subject tests negative for anti-malarial antibodies, he will be further administered the main informed consent form.

Following the signing of the main informed consent for the actual study participation, the relevant study related activities and screening procedures will be undertaken. The subject's demographic data, medical history and concomitant medication history will be recorded at screening/baseline. All subjects included in screening will undergo a detailed physical examination (including vital signs) as well as all protocol-defined laboratory assessments for the screening period (D-14 through D-1).

Informed consent process will include counselling about birth control measures for male subjects by the Investigator team. Results of HIV, Hepatitis B, and Hepatitis C virus infection will be reported in a confidential manner to the study subject only and will not be reported to anyone outside of the study.

A complete review of inclusion/exclusion criteria will be conducted and subjects in whom all inclusion criteria and no exclusion criteria are met, will be enrolled in the study if in good health as judged by physical examination and medical history and will be given a unique randomisation number.

The protocol-defined screening period is 14 days. In case, a subject exceeds this defined screening period (D-14 through D-1), then the subject will have to be re-screened keeping the same screening number. This subject will undergo all the screening procedures again prior to eligibility check and study entry; however the previously done pre-screening procedures and the pre-screening as well as main informed consents will be considered valid at the time of this re-screening. Apart from this, no retest for any abnormal laboratory parameters reported during the screening period will be allowed.

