### 7.2.7 Laboratory Safety Assessments

Laboratory assessments will be done to assess biological safety at 28 days after each vaccination in reference with the baseline before the first dose, by measuring the following:

- Haematology: RBC count, Haemoglobin\*, Haematocrit/Packed Cell Volume (PCV), MCV (Mean Corpuscular Volume), MCH (Mean Corpuscular Haemoglobin), MCHC (Mean Corpuscular Haemoglobin Concentration), Platelet Count and Total Leukocyte Count (TLC) along with Differential Leukocyte Count (DLC) on Days -14, 28, 56, 180, 208, 365.

\*If the haemoglobin drops below 13 gm/dL, then a direct Coomb's test and a peripheral blood smear/film will be prepared and examined for evidence of possible haemolysis

*Information contained in this publication is the property of EVI and ICGEB and is confidential and will not be disclosed to third parties without written authorization from EVI and ICGEB. No part of this document may be reproduced, stored in a retrieval system or transmitted in any form or by any means -electronic, mechanical, recording or otherwise - without the prior authorization of EVI and ICGEB*

[figure not shown][figure not shown]

- Serum Chemistry: Potassium, Sodium, AST, ALT, Direct, Indirect and Total Bilirubin, Alkaline Phosphatase, Gamma Glutamyl Transpeptidase ( $\gamma$ GT), Creatinine, and Random blood glucose on Days -14, 28, 56, 180, 208, 365
- The total amount of blood sample required for these assessments across all visits would be approximately 60 ml.
- For all the laboratory evaluations, the investigator will receive the results/reports as per specified timelines from receipt of specimen at DLS (provided acceptable specimens and/or requisition forms have been obtained).
- The Sponsor's Medical Monitor will be alerted about any value significantly outside the normal range (Refer to the DLS Laboratory Manual for details).
- The screening (D-14 through D-1) and post-vaccination safety laboratory evaluations will be performed at the Central Laboratory at DLS, Mumbai, India.

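### The per-dose laboratory safety endpoint names only the pre-first-dose screening value as reference; the pre-vaccination samples of Days 28 and 180 should be added as a second reference for doses 2 and 3

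*Supplement*

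**What the plan says.** - **Reference.** Section 4.6.1 lists among the primary safety criteria "Biological safety, 28 days after each vaccination, in reference with the baseline before the first dose, by measuring the following parameters". Section 7.2.7 repeats it: "Laboratory assessments will be done to assess biological safety at 28 days after each vaccination in reference with the baseline before the first dose". The synopsis and the opening of Section 7.2 agree.
- **What the baseline is.** Footnote 9 to Table 1 says: "Haematology assessments done at Screening Visit (Visit 2) will be considered as screening laboratory assessments for eligibility as well as baseline assessments for safety end-points". Footnote 10 says the same of serum chemistry. Neither panel is drawn on Day 0.
- **The gate.** That draw had to satisfy exclusion criteria 9 and 10 in Section 5.4.2, for example "Subjects will be excluded if AST > 40 IU/L, ALT > 41 IU/L". A full re-screen is possible if the 14-day screening period is exceeded. Section 7.1 then adds: "Apart from this, no retest for any abnormal laboratory parameters reported during the screening period will be allowed".
- **Pre-dose samples.** Footnotes 9 and 10 also say "Blood samples for haematology will be collected prior to vaccination on Days 28 and 180" and "Blood samples for serum chemistry will be collected prior to vaccination on Days 28 and 180". No section makes these the reference for dose 2 or dose 3.
- **Analysis.** Section 11.5.1.3 tabulates laboratory results by vaccine group at each time point, as raw values and as position against the normal range. It specifies no change from baseline. New or worsened laboratory abnormalities are to be reported as adverse events, but the value they are compared with is not named. For pre-existing disease, the rule for counting an event as emergent looks only at what was ongoing at the first visit.

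**The concern.** The endpoint is worded dose by dose, but after doses 2 and 3 its reference predates all vaccination. Two things then mix with any effect of the dose in question.

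First, an abnormality that arose before dose 3 and was visible on Day 180 counts as a departure from baseline 28 days after dose 3. Second, the reference is one measurement that had to pass an entry limit. Subjects whose screening value fell below their usual level are kept, and those whose value rose above the limit are removed. Later readings therefore drift back across the limit with no vaccine effect.

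With 10 subjects per test arm in a first-in-human study, one or two excursions shape how a dose level reads. Showing whether an excursion preceded the dose needs the same subject's pre-dose value beside the post-dose value. The trial collects both, but the plan does not pair them.

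**Working it through.** The plan gives no figure to reproduce: Section 11.1.1 says no sample size calculation was done, and no analyte variability is stated.

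**Timing** (Table 1, visit windows ignored). Screening falls between Day -14 and Day -1.

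| Reading | Age of screening value | Age of pre-dose sample |
|---|---|---|
| Day 56 (after dose 2) | 56+1 = 57 to 56+14 = 70 days | 56-28 = 28 days |
| Day 208 (after dose 3) | 208+1 = 209 to 208+14 = 222 days | 208-180 = 28 days |

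**Simulation, ALT, no vaccine effect.**
- From the plan: entry limit 41.
- Assumed: log-normal values, median 24 U/L, between-person CV 40%, within-person CV 15%, 20% or 30%.
- Model: ln(value) = person level + visit error, each with SD = sqrt(ln(1+CV²)). That gives 0.385 between persons and 0.149, 0.198 or 0.294 within.
- Two million subjects per scenario. Only those with a screening value of at most 41 are kept.

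Let A be the share above 41 at Day 208; all of these are new relative to screening. Let B be the share above 41 at Day 208 but not on Day 180. The share already abnormal before dose 3 is 1 - B/A.

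| Within-person CV | A | B | 1 - B/A |
|---|---|---|---|
| 15% | 0.0385 | 0.0237 | 38% |
| 20% | 0.0532 | 0.0342 | 36% |
| 30% | 0.0847 | 0.0576 | 32% |

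**In subjects.** In an arm of 10 the two references differ by 10 × (0.0385 - 0.0237) = 0.15 to 10 × (0.0847 - 0.0576) = 0.27 of a subject on this one analyte.

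**Mean change to Day 208.** Against screening the bias is +1.0% to +4.6%; against Day 180 it is zero. The standard error of the mean log change with n = 10 is 6.6% to 12.7%, so the bias is 1.0/6.6 = 0.16 to 4.6/12.7 = 0.36 of a standard error.

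**Any time.** The share above 41 at one or more of Days 28, 56 and 208 is about 8% to 18.6% against screening. With Day 56 referred to Day 28 and Day 208 to Day 180, it is 7.6% to 17.7%. It barely moves, because for dose 1 the screening value is the pre-dose value.

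**Second set of assumptions.** Used here: ln ALT with median 25 U/L and SD 0.45; haemoglobin 14.8 g/dL with SD 1.1; within-subject correlation 0.5 to 0.9.
- New ALT excursions at Day 208: 9.9% to 4.5% against screening, 7.2% to 2.7% against Day 180.
- Haemoglobin outside 13 to 18 g/dL: 4.2% to 2.1% against screening, 3.4% to 1.3% against Day 180.
- The screening reference thus gives about 1.2 to 1.7 times as many new excursions.
- The mean shift is at most about 6% for ALT and 0.06 g/dL for haemoglobin.

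**Controls.** With the haemoglobin gate and an assumed common drift of -0.3 g/dL, the mean change was -0.33 in test and in control subjects, difference 0.00. The 95% half-width of that difference is t × sqrt(1/n1 + 1/n2) in SDs of change: 1.18 for 10 against 5, and 0.84 for 10 against all 15 controls.

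**The case against.** The strongest reply is that nothing is hidden. Section 11.5.1.3 tabulates every time point, so Day 180 stands beside Day 208. The randomised controls pass the same gate on the same schedule. The first-dose baseline is the proper reference for cumulative toxicity, because Days 28 and 180 already carry effects of earlier doses. Section 11 also leaves full detail to a separate SAP, which is not shown.

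Much of this stands. A reader might infer that laboratory safety is judged only against screening; the tabulation at every time point contradicts that. A reader might infer that drift and regression to the mean are charged to the later dose. No section contains such a rule: causality is the investigator's judgement, and an unchanged Day 180 abnormality need not be called new. A general spurious rise in enzymes and bilirubin is not shown either. Only ALT and haemoglobin were modelled, and the bilirubin entry limits (1.2 total, 0.4 direct) are wider than the reference ranges in Appendix B (0.99 and 0.30), so the ALT result does not carry over.

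Three things remain:
- Group tables at separate time points cannot show whether the same subject was abnormal before the dose.
- The controls remove the bias only with poor precision, and Section 11.5.1 says the sample size allows no comparison between groups.
- The reference is a rule stated in the endpoint definition, not detail awaiting an SAP, and an SAP would inherit it.

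**Conclusion.** The point holds in a limited form. For doses 2 and 3 the endpoint names a reference that is the gated screening value, 57 to 70 days old at Day 56 and 209 to 222 days old at Day 208. The 28-day-old pre-dose samples are given no role.

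Under the assumed ALT parameters and no vaccine effect, about one third of the Day 208 values newly above the limit relative to screening were already above it on Day 180. The bias in mean change is well under half a standard error for an arm of 10 and is common to both randomised arms. The gain therefore lies in reading individual excursions by dose, not in correcting means. Every analyte distribution here is assumed; only the entry limits and the schedule come from the protocol. This is a cheap improvement to a primary safety endpoint, not an error that invalidates it.

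**What to change.** - In 4.6.1 and 7.2.7, keep the pre-first-dose baseline for cumulative effect, and name the Day 28 and Day 180 pre-vaccination samples as a second reference for doses 2 and 3.
- In 11.5.1.3, add within-subject change and shift tables of Day 56 against Day 28 and Day 208 against Day 180, beside those against screening, by vaccine group including controls.
- In 11.5.1.3, state that new or worsened laboratory abnormalities are reported against both references.
- Do not add a rule that removes attribution to the vaccine when an abnormality was already present on Day 180. It may be carried over from an earlier dose.

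The cost is wording in three sections and extra table columns. No visit, sample or subject is added.

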### 4.6.2 Secondary Endpoint(s)

- The humoral response to the candidate vaccine antigen will be assessed (quantitative assessment) by measuring the level of IgG antibodies developed against PfMSP-119 and Pff2 by ELISA on Days 0, 28, 56, 180, 208 and 365
- The humoral response to the candidate vaccine antigen will be assessed (qualitative assessment) to verify the ability of the IgG antibodies developed against PfMSP-119 and Pff2 to recognise the native proteins, namely, PfMSP1 and EBA175 in late stage *P. falciparum* schizonts and merozoites by IFA on Days 0, 28, 56, 180, 208 and 365.

### 4.6.3 Exploratory Endpoint(s)

- The quality of the humoral immune response will be additionally assessed by measuring the following:

*Information contained in this publication is the property of EVI and ICGEB and is confidential and will not be disclosed to third parties without written authorization from EVI and ICGEB. No part of this document may be reproduced, stored in a retrieval system or transmitted in any form or by any means -electronic, mechanical, recording or otherwise - without the prior authorization of EVI and ICGEB*

[figure not shown][figure not shown]

- IgG1, IgG2, IgG3, IgG4 subclasses by ELISA on samples obtained at Days 0, 28, 56, 180, 208 and 365.
- The ability of the IgG antibodies to block homologous and heterologous parasite growth *in vitro* by a *P. falciparum* blood-stage growth inhibition assay (GIA) against three parasite strains on samples obtained at Days 0, 56, 208 and 365

*Information contained in this publication is the property of EVI and ICGEB and is confidential and will not be disclosed to third parties without written authorization from EVI and ICGEB. No part of this document may be reproduced, stored in a retrieval system or transmitted in any form or by any means -electronic, mechanical, recording or otherwise - without the prior authorization of EVI and ICGEB*

[figure not shown][figure not shown]

### 5.3 Number of Subjects

- A sufficient number of subjects will be screened to enrol a total number of 45 subjects in the study.
- 30 subjects will receive the investigational vaccine (i.e. JAIVAC-1—Montanide ISA 720) with 10 subjects in each cohort and
- 15 subjects will receive the control vaccine (i.e. Hepatitis B vaccine) with 5 subjects in each cohort.

Subjects who are discontinued from the study prior to the first vaccination will be replaced. However, subjects who are discontinued from the study after the first vaccination will be considered as drop-outs and will not be subsequently replaced.

### 5.4 Target Population

The study will be performed in healthy male Indian volunteers aged 18 to 45 years (both inclusive). The Investigator must ensure that all subjects who meet the inclusion and exclusion criteria during screening period (D-14 through D-1) and / at baseline (Day 0) (as applicable) are offered enrolment in the study. No additional exclusions can be applied by the Investigator, in order that the study population will be representative of all eligible subjects.

#### 5.4.1 Inclusion Criteria

*To be eligible to participate in the study, the subjects should fulfil all of the following inclusion criteria at the time of the Screening/ Baseline Visit:*

1. Male subject aged 18 to 45 years (both inclusive)
2. Subject with general good health based on the medical history and clinical examination

*Information contained in this publication is the property of EVI and ICGEB and is confidential and will not be disclosed to third parties without written authorization from EVI and ICGEB. No part of this document may be reproduced, stored in a retrieval system or transmitted in any form or by any means -electronic, mechanical, recording or otherwise - without the prior authorization of EVI and ICGEB*

[figure not shown][figure not shown]

3. Subject must be willing to sign the Informed Consent Form
4. Subject must be reachable by phone during the entire study period (12 months)
5. Subject must be capable and willing to complete and return diary cards and to attend all follow-up visits
6. Male subject must agree to use one of the following medically-acceptable birth control measures throughout the duration of the study (birth control counselling and measures will be provided by sites as required)

Double barrier method (e.g. condom with spermicidal jelly) used for the entire study period

Or

Should be Surgically sterile (vasectomy)

